## Abstract

**Introduction:**

Partner notification (PN) is a process aiming to identify, test and treat the sex partners of people (index patients) with sexually transmitted infections (STIs). Accelerated partner therapy (APT) is a PN method whereby healthcare professionals assess sex partners, by telephone consultation, before giving the index patient antibiotics and STI self-sampling kits to deliver to their sex partner(s). The Limiting Undetected Sexually Transmitted infections to RedUce Morbidity programme aims to determine the effectiveness of APT in heterosexual women and men with chlamydia and determine whether APT could affect *Chlamydia trachomatis* transmission at population level.

**Methods and analysis:**

This protocol describes a cross-over cluster randomised controlled trial of APT, offered as an additional PN method, compared with standard PN. The trial is accompanied by an economic evaluation, transmission dynamic modelling and a qualitative process evaluation involving patients, partners and healthcare professionals. Clusters are 17 sexual health clinics in areas of England and Scotland with contrasting patient demographics. We will recruit 5440 heterosexual women and men with chlamydia, aged ≥16 years.

The primary outcome is the proportion of index patients testing positive for *C. trachomatis* 12-16 weeks after the PN consultation. Secondary outcomes include: proportion of sex partners treated; cost effectiveness; model-predicted chlamydia prevalence; experiences of APT.

The primary outcome analysis will be by intention-to-treat, fitting random effects logistic regression models that account for clustering of index patients within clinics and trial periods. The transmission dynamic model will be used to predict change in chlamydia prevalence following APT. The economic evaluation will use mathematical modelling outputs, taking a health service perspective. Qualitative data will be analysed using interpretative phenomenological analysis and framework analysis.

**Ethics and dissemination:**

This protocol received ethical approval from London—Chelsea Research Ethics Committee (18/LO/0773). Findings will be published with open access licences.

**Trial registration number:**

ISRCTN15996256.

Strengths and limitations of this studyThe trial will evaluate accelerated partner therapy (APT), a novel approach to partner notification (PN), designed to facilitate and accelerate testing and treatment of sex partners of people with chlamydia.The primary outcome, chlamydia positivity, is objectively measured and clinically relevant, given its negative impact on both individual health outcomes and NHS (National Health Service) costs.This clinic-wide low-risk intervention has been granted ethical approval at the service-level without need for individual consent and complies with GDPR (General Data Protection Regulation).The pragmatic trial design will ensure that the effectiveness of APT is evaluated under real-life clinical conditions.An integral process evaluation will capture any variations in the operationalisation of PN and APT at the local level and enable optimisation of APT procedures in any future roll-out.

## Introduction

Partner notification (PN) is the process of identifying, testing and treating sex partners of a person with a sexually transmitted infection (STI).^1^ PN is a key element of STI control on several levels.^2^ It should benefit the individual diagnosed with the STI (the index patient) by preventing re-infection, the sex partner who might be the source of infection or could transmit undiagnosed infections to new sexual partners, and it should help to reduce spread of STIs in sexual networks and populations.

STIs are a major public health concern. The sexually transmitted pathogen *Chlamydia trachomatis* causes chlamydia infection, the most commonly reported bacterial STI in Britain,^3–5^ with 218 095 diagnosed cases in England in 2018.^3^ Untreated chlamydial infection can lead to pelvic inflammatory disease (PID), infertility, ectopic pregnancy and chronic pelvic pain in women.^6^ In prospective studies with active follow-up, about 20% of women have a repeat diagnosis of chlamydia infection in the year after treatment.^7–9^

Chlamydia screening programmes aim to reduce the occurrence of complications by detecting and treating infections. For example, the incidence of diagnosed chlamydia in England has increased because of increases in both testing and transmission.^3 10–12^ Chlamydia control activities in England include a National Chlamydia Screening Programme, which offers chlamydia testing to sexually active adults aged under 25 years, who accounted for 61% of diagnosed chlamydia infections in 2018.^13^ The Public Health Outcomes Framework in England sets targets to increase chlamydia diagnosis in young men and women.^14^ However a mathematical modelling study suggested that improving PN outcomes for chlamydia would be more cost effective than increasing the coverage of chlamydia testing,^2^ emphasising the importance of optimising the effectiveness of PN whatever the coverage of testing.

Like many other bacterial STIs, chlamydia does not induce lasting immunity after antibiotic treatment, and this represents a particular challenge for STI control efforts. Repeated infection after treatment can result from re-infection from an untreated partner, indicating failed PN, or from a new infection from a new partner. Alternatively, infection might persist if antibiotic treatment is not effective for any reason. It is usually not possible to determine the reason for the repeat positive test (re-infection, new infection or treatment failure). In a mathematical modelling study, the peak incidence of repeated infections was estimated at 2–5 months after treatment.^15^

Given the importance of PN in the control of STIs such as chlamydia, there is a need to optimise sexual health services’ support for effective PN. Currently, healthcare professionals in British sexual health services often struggle to meet modest targets.^16–18^ The PN process is challenging both for patients who may face barriers to informing sex partner(s) about the STI, and to services where trained staff need time to elicit sensitive information from patients in order to support PN.

Offering patients alternatives, so that they can choose the most acceptable PN method—which might differ between sex partners—is considered optimal practice.^19^ For people with chlamydia, PN is most often performed through patient referral,^20 21^ in which a healthcare professional advises the person with a diagnosed infection (the index patient) to inform their sex partner(s) of the need for testing and treatment and to refer them to a sexual health service (simple patient referral). This basic advice can be supplemented by information, in the form of written leaflets or website addresses, for the index patient to give to their partner(s) (enhanced patient referral). Expedited partner therapy (EPT) is a strategic approach to enhanced patient referral, widely adopted in USA, in which a healthcare professional gives the index patient antibiotics or a prescription for their partner(s).^22^ A systematic review found that EPT results in lower proportions of index cases with repeated curable STIs than simple patient referral,^16^ and a US study demonstrated decreases in chlamydia positivity and gonorrhoea incidence at the population level.^23^ However, EPT, as now widely practised in USA, does not require a consultation with the sex partner and does not comply with UK prescribing guidance,^24^ so cannot be implemented in UK.

We therefore developed accelerated partner therapy (APT) as an adaptation of EPT to speed up the enhanced patient referral process.^25–27^ APT complies with UK prescribing guidance since a healthcare professional assesses the appropriateness of the prescribed antibiotics for the partner.^28^ In brief, the healthcare professional performs a telephone consultation with the sex partner in private during the index patient’s clinic attendance. If medically safe, the index patient receives an APT pack, containing antibiotics and self-sampling kits for STI and HIV to deliver to their sex partner(s), or the clinic may post the APT pack to the sex partner(s). In pilot studies, APT resulted in faster sex partner treatment and greater overall numbers of sex partners treated, when compared with standard PN, but lower levels of testing for HIV and other STIs, when offered without HIV testing as part of the pack.^25 26^

In the trial described here, we aimed to compare strategies for PN, specifically APT with routine PN approaches as currently practised in UK. As part of the Limiting Undetected Sexually Transmitted infections to RedUce Morbidity (LUSTRUM) programme (lustrum.org.uk), we designed a randomised controlled trial (RCT) to determine the effects of APT for people with *C. trachomatis* on biological, as well as patient-reported clinical outcomes. Specific objectives are to determine: (1) the effect of APT on the proportion of index patients who test positive for chlamydia 12–16 weeks after the PN consultation; (2) the effect of APT on the proportion of sex partners treated; (3) the cost effectiveness of APT on long-term sexual and reproductive health outcomes, based on a linked transmission dynamic modelling study; (4) the effects of APT according to sex partner type; (5) whether APT is associated with faster treatment than standard PN; (6) the effects of APT on transmission of chlamydia at the population level, based on mathematical modelling; and to conduct: (7) a comprehensive process evaluation to understand the experiences of healthcare professionals, patients and sex partners of APT.

## Methods and analysis

### Trial design

LUSTRUM is a cross-over cluster RCT of APT offered as an additional PN method compared with standard PN alone. The APT intervention is offered at the level of the sexual health clinic, with randomisation of each clinic to either intervention or control arm in the first phase of the trial. The trial design is summarised in figure 1.

**Figure 1 F1:**
[figure not shown]
Index patient and sex partner pathways during control and intervention arms. *Random allocation to intervention or control arm in the first phase of the trial. †Index patients and sex partners are notified of results via two pathways: (1) negative results: individual receives a text from The Doctors Laboratory; (2) positive/equivocal results: individual receives results directly from clinic. APT, accelerated partner therapy; HCP, healthcare professional; LUSTRUM, Limiting Undetected Sexually Transmitted infections to RedUce Morbidity; PN, partner notification.

### Settings

Seventeen NHS (publicly funded, free to access) specialist sexual health clinics (clusters) across England and Scotland with high volumes of positive *C. trachomatis* test results and with contrasting patient demographics. Clinics were selected from those expressing interest, based on numbers of reported chlamydia diagnoses data in the Public Health England Genitourinary Medicine Clinical Activity Dataset for STI surveillance (England) and geographical diversity (Scotland) to create three strata: London, non-London metropolitan ‘cities’ and non-London urban ‘towns’. A full list of study sites is included in the Acknowledgments.

### Eligibility criteria for index patients

Aged 16 years or older, positive test for *C. trachomatis* and/or clinical diagnosis of PID or cervicitis (women) or non-gonococcal urethritis (NGU) or epididymo-orchitis (men) and report at least one contactable sexual partner in the past 6 months. Index patients with PID, cervicitis, NGU and epididymo-orchitis whose test results are subsequently found to be negative for *C. trachomatis* will not be included in statistical analysis. Exclusion criteria are: groups of patients with more complex PN requirements; co-infection with other STIs including HIV, men who have had sex with men in the past 6 months, and patients who have paid for or who have been paid for sex in the past 6 months. Patients with any clinical, social or other circumstances, such as sexual assault or insufficient English language skills to safely engage in telephone consultations, which emerge during the face-to-face consultation and make APT unsuitable will also be excluded.

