Box 1Overview of accelerated partner therapy (APT) for index patientsIndex patient has partner notification (PN) consultation with healthcare professional (HCP); HCP assesses eligibility for APT.Eligible index patient is offered APT alongside the clinic’s other standard PN options. The patient can choose different methods for different partners.Index patient telephones or messages sex partner (with or without the HCP present, according to preference) to offer immediate telephone assessment by the HCP.Index patient waits in clinic while the HCP conducts APT telephone consultation in private with sex partner.Index patient is informed that they will receive a follow-up telephone call in 2 weeks and they will either receive a chlamydia self-sampling postal kit in 12–16 weeks (preferred), or they may re-attend the clinic for testing.Two-week follow-up: research health adviser (RHA) telephones index patient to find out about PN outcomes with partner(s), to remind them of the repeat test, and to invite them to be contacted about taking part in a telephone interview regarding their experiences of APT (process evaluation).12 weeks: index patient is sent a personalised text reminder about repeat test.13 weeks: index patient is sent a self-sample kit by The Doctors Laboratory (TDL). Index patient returns self-collected sample or attends clinic for repeat testing. S/he receives results either via text message from TDL (negative results) or using routine clinic systems (positive or equivocal results). Positive results are managed according to routine clinic protocol. If the index patient does not return a self-sample or attend clinic for repeat testing, they receive a personalised text reminder 8 days after the self-sample kit is sent out, followed by a telephone call from the RHA 13 days after the self-sample kit is sent out. Self-samples received >24 weeks post-PN interview are excluded.

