### Control

During the control phase, each clinic follows their usual protocols for standard PN. All clinics conduct enhanced patient referral, including verbal information about notifying partners plus additional information (written leaflets or signposting to a website). The healthcare professional will occasionally notify partners on behalf of the patient, if requested. Follow-up telephone calls and repeat testing will be the same as those during the APT phase.

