### Recruitment

During the initial PN consultation with the index patient, the healthcare professional will assess eligibility for the study for all patients with a laboratory positive test result for chlamydia or a clinical diagnosis of NGU/epididymo-orchitis (men) or PID/cervicitis (women). During the intervention phase, the healthcare professional will offer eligible patients APT in addition to standard methods of PN. The trial data manager will monitor recruitment and patient uptake of the APT intervention throughout the trial period supplying monthly recruitment figures to the Trial Management Group (TMG) and Data Monitoring Committee (DMC).

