### Blinding

Blinding of allocation will not be possible for healthcare professionals, patients or research staff. A statistician blinded to allocation will replicate the analysis of the primary outcome.

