#### Exclusions from analyses

The intervention is implemented at the clinic level and applied to all eligible patients with service-level, rather than individual, consent. Patients can opt-out of their data being used for research (see online supplementary file 1). Once a clinic has begun the allocated intervention then all eligible patients added to the RELAY web tool will be included in analysis, following the spirit of an intention-to-treat analysis and the all-randomised population. However, in the unlikely event of a substantial period in which any clinic is subsequently unable to implement the intervention for any reason then we will also conduct an analysis that only includes patients attending the clinic while it is able to offer the intervention, in the spirit of a per-protocol analysis and a protocol compliant population. The inclusion of patients in analysis will not be influenced by whether the patient does or does not take up the offer of APT.

10.1136/bmjopen-2019-034806.supp1Supplementary data

Patients who present with conditions managed at first attendance as presumptive urogenital chlamydia but who subsequently are found to have negative chlamydia tests will be excluded from analyses.

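### Study entry depends on an open-ended judgement of APT suitability, made by unblinded staff after clinic allocation, so the two arms may be selected differently

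*Protocol article*

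**What the plan says.** Under Eligibility criteria for index patients, the article lists fixed exclusions (co-infection, men with recent male partners, paid sex). It then adds a discretionary one: patients with clinical, social or other circumstances "which emerge during the face-to-face consultation and make APT unsuitable will also be excluded". Sexual assault and English too limited for telephone consultations are given as examples, not as a closed list.

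Under Recruitment, "the healthcare professional will assess eligibility for the study for all patients with a laboratory positive test result for chlamydia" or a qualifying clinical diagnosis. The next sentence applies to one phase only: "During the intervention phase, the healthcare professional will offer eligible patients APT in addition to standard methods of PN". Under Blinding, "Blinding of allocation will not be possible for healthcare professionals, patients or research staff". Under Exclusions from analyses, once a clinic has begun its allocated condition, "all eligible patients added to the RELAY web tool will be included in analysis".

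In the Intervention section, Box 1 has the step "HCP assesses eligibility for APT" ahead of the offer. That section also says that a patient for whom APT stops being feasible is offered standard PN instead. Under Control, "each clinic follows their usual protocols for standard PN", with no APT assessment mentioned.

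**The concern.** Clinics are allocated before patients are identified. The Randomisation section protects the clinic allocation with three separate people, but the article describes no comparable protection for the patient-level decision on who is eligible.

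That decision turns on fitness for one arm's intervention, and on circumstances that come to light in conversation. A conversation that leads to an offer of APT may bring out more such circumstances than one about usual PN. If so, the two phases of the same clinic would enter different mixes of patients, and the primary odds ratio would move without any treatment effect. The Outcomes section reads a repeat positive test as re-infection from an untreated partner only on the assumption that other reasons for a positive test are balanced between arms. Unequal selection would undermine that assumption.

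**Working it through.** **Does the judgement set the denominator?** Yes. Only eligible patients entered in RELAY are analysed, and APT suitability is part of eligibility. The exclusion therefore acts after allocation and before the intention-to-treat set is formed.

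**Do the stated safeguards reach it?**
- Inclusion in analysis does not depend on uptake of APT. This covers patients who are offered APT and decline, not patients judged unsuitable.
- Patients for whom APT is no longer feasible stay in and receive standard PN. The article does not say how such a patient is told apart from an unsuitable one.
- Cross-over balances stable differences between clinics, not different selection between phases within a clinic.
- Covariate adjustment helps only for measured factors. Multiple imputation addresses missing outcomes among included patients. Neither recovers patients never entered.

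**How large could it be?** The protocol gives no figure for the share judged unsuitable or for their risk, so there is no stated figure to reproduce. Both inputs below are assumptions:
- *c* = positivity among all otherwise eligible patients: 10% or 25%, the ends of the control-arm range in the Sample size section.
- *f* = share judged APT-unsuitable (assumed).
- *r* = their risk of a positive repeat test relative to the others (assumed).
- No true effect of APT.

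Risk in suitable patients: *s* = *c* / (1 − *f* + *f r*). If all unsuitable patients are excluded in the intervention phase and none in control, OR = [*s*/(1 − *s*)] / [*c*/(1 − *c*)].

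Example: *c* = 0.10, *f* = 0.10, *r* = 2 gives *s* = 0.10/1.10 = 0.0909 and OR = 0.1000/0.1111 = 0.90.

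| *f* | *r* | *s* (*c* = 10%) | OR | *s* (*c* = 25%) | OR |
|---|---|---|---|---|---|
| any | 1 | 10.0% | 1.00 | 25.0% | 1.00 |
| 5% | 1.5 | 9.8% | 0.97 | 24.4% | 0.97 |
| 10% | 2 | 9.1% | 0.90 | 22.7% | 0.88 |
| 20% | 2 | 8.3% | 0.82 | 20.8% | 0.79 |
| 10% | 3 | 8.3% | 0.82 | 20.8% | 0.79 |
| 10% | 0.5 | 10.5% | 1.06 | 26.3% | 1.07 |
| 20% | 0.5 | 11.1% | 1.13 | 27.8% | 1.15 |

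A more extreme corner, *f* = 20% with *r* = 3, gives 0.69 and 0.65.

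**If control staff apply half the exclusions:** the unsuitable share left in control is *h* = (*f*/2)/(1 − *f*/2), and control risk is *s*(1 − *h* + *h r*). With *c* = 10% and *r* = 2:
- *f* = 10%: *h* = 0.0526, control risk 0.0957, OR 0.945.
- *f* = 20%: *h* = 0.1111, control risk 0.0926, OR 0.89.

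With equal exclusion in both phases the OR is 1.00.

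**Against the design effects:** 10% to 5% is an OR of (0.05/0.95)/(0.10/0.90) = 0.47, and 25% to 17% is 0.61. For *f* = 10%, *r* = 2, full exclusion in the intervention phase only, the spurious difference is 0.91/5 = 18% of the first target and 2.27/8 = 28% of the second.

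**False-positive rate:** take 17 clinics with 160 × 0.5 × 0.6 = 48 analysed per clinic per phase, coefficient of variation 0.5 and ICC 0.02. The design effect is 1 + (1.25 × 48 − 1) × 0.02 = 2.18, so the effective size is 17 × 48/2.18 = 374 per arm. The two-sided 5% test would then reject about 7% of the time at *c* = 10% and 11% at *c* = 25%. This treats the trial as a parallel design, as the protocol's own calculation does. The extra precision of the cross-over would raise both rates.

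**The case against.** A reader might infer that the exclusion operates only in the intervention phase, and hence that the arms *are* selected differently. The documents do not support that. The Recruitment section has eligibility assessed for all patients, without limiting it to one phase, and the eligibility section gives one definition for the whole trial.

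A reader might also suppose that the call to the partner is what triggers the exclusion. Box 1 puts the eligibility assessment before any contact with the partner. Problems at later steps lead to standard PN or, for the partner, advice to attend clinic. They do not remove the index patient.

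The named examples weaken the concern further. Limited English is apparent face to face in either phase, and it matters in control too because follow-up calls are the same. Nothing in the article says that excluded patients have a higher repeat-infection risk. Restricting both arms to patients who could be offered APT is also a legitimate target population. Figure 1, which shows the pathways in both arms, was not available for this review, and operational detail on screening may sit in the full protocol.

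All of this stands, and it reduces the point from a demonstrated bias to a risk. It does not remove the risk. The criterion is open-ended, is defined by one arm's intervention, is judged by staff who know the phase, and decides who is analysed. The defence of the target population holds only if the rule works equally in both phases, and a rule that depends on what emerges in conversation gives weak assurance of that.

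**Conclusion.** The point holds as a plausible risk of differential selection, not as a fact established by the text. Direction and size are unknown. The spurious OR would favour APT if the excluded patients have higher repeat positivity, go against APT if lower, and be 1.00 if risks or exclusion rates are equal. For assumed unsuitable shares of 5% to 20% and risk ratios of 0.5 to 2, with exclusion in one phase only, it lies at about 0.8 to 1.1 (up to 1.15 at 25% positivity). It moves towards 1 as control staff apply more of the exclusions. Biases of this size are well short of the design effects but large enough to matter to a result near the margin. A change is worth making because the rule is stated in the protocol and a less exposed one is available at small cost.

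**What to change.** - Define the primary analysis set by facts that can be ascertained identically in both phases: age, *C. trachomatis* positive, at least one contactable partner, and the fixed co-infection, male-partner and paid-sex exclusions.
- Record APT suitability in RELAY in both phases, before the PN method is discussed.
- Treat unsuitability as a reason not to offer APT, and keep these patients in the intention-to-treat set.
- Report exclusions, and chlamydia-positive patients not entered, with reasons and by phase. Reporting alone would reveal unequal selection but not prevent it.

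The cost is one eligibility sentence, one RELAY field and slight dilution. If 10% of intervention-phase patients are retained without being offered APT, have the same baseline risk and gain nothing, a 5-point difference becomes 0.9 × 5 = 4.5 points. Whether particular patients should be contacted for follow-up is for the investigators to decide. Whatever rule they adopt should be the same in both phases, or the selection would return as missing outcomes.
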